#### Sharing of water sources with animals

This outcome only applies to the subgroup of individuals in the sample who report that their household owns any animals. It is a binary indicator of whether animals can access and drink from the same source of water used by the participant’s household to drink and cook with. This was determined via visual inspection by the data collectors. This outcome is to allow us to explore whether the CDs may decease the relative frequency of such water sharing within households, which is one focal issue in the CDs.

#### Awareness of the benefits of not feeding healthy animals antibiotic-containing feed

This outcome is only collected from the subgroup of individuals in the sample who report being aware of what an antibiotic is and being aware of ABR. It is a binary indicator of whether the participant is aware that you can reduce the spread of antibiotic resistant infections by not feeding health animals feed containing antibiotics. Specifically, whether the participant responds “yes” as opposed to “no” or “do not know” to the question “Can you help to stop the spread of antibiotic resistant infections by not giving healthy animals feed containing antibiotics?” This outcome is to allow us to explore whether the CDs may improve simple reported awareness of the appropriate behavior in relation to this increasingly common but inappropriate animal-health related practice.

### Sample size

Due to logistical constraints around how many intervention clusters we believed we can implement in, we decided that we could have a maximum of 25 clusters per treatment group. As we plan to sample participants from two villages per cluster, and as we plan to sample an equal number of female and male participants per village, we also decided to sample an even number of participants per cluster. Following discussion among the trial team we decided that for both primary outcomes we would look at cluster-level treatment effects (40), which will mean aggregating the outcome to the cluster level by computing the mean of all survey participants’ percentage knowledge scores for each cluster (which we refer to as the cluster-level mean percentage knowledge score below). Based on discussion among the trial team we targeted being able to detect if the cluster-level mean percentage knowledge score for both outcomes was 15 percentage points or greater in the intervention group compared to the control group. We conservatively assumed an intracluster correlation coefficient of 0.3 for both primary outcomes, based on some related data from this setting in our previous survey study (14). We used the approach of Horzo to estimate plausible values for the overall variance for each primary outcome (41): 40 for the knowledge score measuring the level of correct and appropriate knowledge about antibiotics, ABR, and usage of antibiotics for human illness, and 25 for the knowledge score measuring the level of correct and appropriate knowledge about usage of antibiotics for animal health and antibiotic-related environmental considerations.

Based on these inputs and using the approach of (42) (based on formula 2 and assuming a cluster-level analysis), we then looked at a range of sample size scenarios. We adjusted the standard alpha level of 0.05 to 0.025, following a Bonferroni approach to account for the multiple testing of two primary outcomes. From these results we will aim to sample 44 participants per cluster (22 per village), so 1,100 participants across 25 clusters per treatment group and 2,200 participants across all 50 trial clusters, for the baseline and endline surveys. Conditional on these assumptions, when comparing between the treatment groups at endline we will have 90% power to detect a 14-percentage-point or greater difference between each group’s mean cluster-level percentage knowledge score regarding correct and appropriate knowledge about antibiotics, ABR, and usage of antibiotics for human illness, and 90% power to detect a 11-percentage-point or greater difference between each group’s mean cluster-level percentage knowledge score regarding correct and appropriate knowledge about usage of antibiotics for animal health and antibiotic-related environmental considerations.

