#### Primary outcome 2: Percentage of correct/appropriate responses to 20 questions assessing correct/appropriate knowledge about usage of antibiotics for animal health and antibiotic-related environmental considerations

Our second primary outcome will also measure individuals’ knowledge but will focus on correct and appropriate knowledge about usage of antibiotics for animal health (e.g., prophylaxis and growth promotion as well as disease) and antibiotic-related environmental considerations. For this outcome we will ask 20 multiple-choice questions, which will be scored in the same way as the previous knowledge outcome and again converted to a percentage for analysis (see *Survey questionnaire* in Supplementary file 2 for a full list of the questions). This outcome will allow us to assess whether the CDs improve the level of correct and appropriate knowledge about the usage of antibiotics for animal health and antibiotic-related environmental considerations (the other main aspects of a One Health perspective on antibiotics and ABR).

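### The 90%-power detectable difference for primary outcome 2 should be about 14 percentage points, not 11; at 11 points the stated inputs give 67–70% power

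*Protocol article*

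**What the plan says.** All the planning inputs are in the Sample size section of the protocol article. On clusters: "we decided that we could have a maximum of 25 clusters per treatment group". On participants: "we will aim to sample 44 participants per cluster (22 per village), so 1,100 participants across 25 clusters per treatment group". On clustering: "We conservatively assumed an intracluster correlation coefficient of 0.3 for both primary outcomes". The overall variance for primary outcome 1 is given as 40. For primary outcome 2 it is "25 for the knowledge score measuring the level of correct and appropriate knowledge about usage of antibiotics for animal health and antibiotic-related environmental considerations". No units are attached to either. Alpha is set at 0.025 to allow for two primary outcomes, and the calculation assumes a cluster-level analysis. The design target is 15 percentage points for both outcomes.

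Conditional on these inputs, the section states 90% power at 14 percentage points for primary outcome 1. For primary outcome 2 it adds "and 90% power to detect a 11-percentage-point or greater difference between each" arm's mean cluster-level score.

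The outcome definitions give the scales. Primary outcome 1 has 25 questions. For primary outcome 2, "For this outcome we will ask 20 multiple-choice questions". Each score is converted to a percentage before analysis.

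**The concern.** Both outcomes share the same number of clusters, cluster size, ICC, alpha and power. The two detectable differences can therefore differ only through the standard deviation on the percentage scale. If the variances are counts of correct answers, those standard deviations are almost identical: √40/25 = 25.3 points and √25/20 = 25.0 points. The detectable differences should then be almost identical too, yet the article gives 14 and 11.

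At stake is an explicit power statement for one of two primary outcomes, and it errs in the favourable direction. A reader would think the trial more sensitive to animal and environment knowledge than to human-use knowledge. That reader could then take a null result as stronger evidence against effects of 11 to 14 points than the planned design supports.

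**Working it through.** **Inputs.** From Sample size: k = 25 clusters per arm, m = 44 per cluster, ICC = 0.3, V = 40 (outcome 1) and V = 25 (outcome 2), alpha = 0.025, power 90%. From the outcome definitions: 25 and 20 questions. Sample size does not say whether the test is two-sided; the analysis sections specify two-sided p-values, so two-sided is used.

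**Formulas.**
- Variance of a cluster mean = V × [1 + (m − 1) × ICC]/m = V × (1 + 43 × 0.3)/44 = V × 13.9/44 = 0.3159 V
- SE of the difference between arms = √(2 × 0.3159 V/25)
- Detectable difference = (z₀.₉₈₇₅ + z₀.₉₀) × SE = (2.2414 + 1.2816) × SE = 3.523 × SE

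**Outcome 1: reproducing the stated figure.** SE = √(2 × 0.3159 × 40/25) = 1.005. Detectable difference = 3.523 × 1.005 = 3.54. As answers out of 25, this is 3.54/25 = 14.2 points. That matches the stated 14 and fixes the scale of the variances as number of correct answers.

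**Outcome 2: same method.** SE = √(2 × 0.3159 × 25/25) = 0.795. Detectable difference = 3.523 × 0.795 = 2.80 answers. On 20 questions, 2.80/20 = **14.0 points**. With t quantiles (48 df, or 44 after removing 4 for the five strata) it is 14.4 points.

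**Where 11 comes from.** 2.80/25 = 11.2 points, using the question count of outcome 1. The ratio of the stated figures, 14/11 = 1.27, is close to √(40/25) = 1.26, as expected if both results were divided by the same number of questions.

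**Power at 11 points for outcome 2.** 11% of 20 questions is 2.2 answers. Power = Φ(2.2/0.795 − 2.241) = Φ(0.526) = 0.70. With the non-central t it is 0.675 (48 df) or 0.673 (44 df). Rounding does not rescue the figure: at 11.49 points power is 74% (normal) or 72% (t).

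**Other readings of the variances.**
- As percentage points squared: 3.5 and 2.8 points.
- 40 and 25 as standard deviations in percentage points: 22.4 and 14.0 points.
- As counts, (25/4)² = 39.1 and (20/4)² = 25, which fit the two printed variances on scales of 0–25 and 0–20.

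**Other settings, variances as counts (outcome 1 / outcome 2, normal quantiles).**
- 90% power, two-sided 0.05 or one-sided 0.025: 13.0 / 12.9 points.
- 90% power, one-sided 0.05: 11.8 / 11.6 points.
- 80% power, two-sided 0.05: 11.3 / 11.1 points. This gives 11 for outcome 2 but contradicts the stated alpha and power and loses the 14 for outcome 1.

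No single setting gives the pair 14 and 11.

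**Target difference.** At 15 points, power for outcome 2 is 94% (normal) or 92% (t).

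**The case against.** The strongest objection is that the units are inferred. The variances appear without units, just after the outcome has been defined as a mean percentage score, and the sources cited for the variances and the formula cannot be seen here. The quarter-of-the-range rule gives 39.1, not exactly 40, for outcome 1. This is fair, but the count reading is the only one found that returns the stated 14, and it gives exactly 25 for a 20-question score.

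A second objection is that the slip could lie elsewhere. If the variance for outcome 2 were 16 on the 0–20 scale (a standard deviation of 20 points), the result would be 11.2 points. A 25-question version of outcome 2 would also give 11.2. Nothing in the article rules these out as history, but each replaces an input that the article prints and on which it makes its power claim conditional. If the authors' records show that a variance or a question count was misprinted, that is the number to correct; either way the printed set cannot stand.

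A third objection is that actual power may be better than 67–70%. The ICC is described as conservative, and the primary analysis adjusts for covariates, including the cluster-level baseline mean. An ICC of about 0.18, or a 38% reduction in the variance of the cluster means (1 − (11/14.0)² = 0.38), would bring the detectable difference to about 11 points. This limits what can be said about achieved power. It does not support the printed figure, which is stated under an ICC of 0.3 and takes no credit for adjustment.

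Finally, little in the design depends on the figure: the target is 15 points, and the article will base its conclusions on estimates and confidence intervals. This bears on how serious the error is, not on whether it is one.

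**Conclusion.** The concern holds. On the article's own inputs, the difference detectable with 90% power for primary outcome 2 is 14.0 percentage points (14.4 with t quantiles), not 11. At 11 points the type II error is 30–33% rather than the stated 10%.

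This rests on reading the variances as squared numbers of correct answers, on a two-sided test at 0.025, and on the printed variance of 25 and question count of 20 being the intended ones. It is an error in a reported power figure; the sample size and the analysis do not depend on it.

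**What to change.** In Sample size, restate the detectable difference for primary outcome 2 as about 14 percentage points (14.4 if t quantiles are used). Add a clause saying that the variances of 40 and 25 are in number-of-correct-answers units, so that the standard deviation is about 25 percentage points for both scores. Before publishing the correction, check the variance and question count for outcome 2 against the original calculation.

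The cost is one number and one clause. The stated sensitivity becomes less favourable, and the number of clusters, the number of participants and the 15-point target stay as they are.

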### Sampling, recruitment and consent

#### Cluster sampling

Across all study subdistricts we have mapped the approximate geographical location of all clusters based on the location of their CCs. Based on our sample size calculation we have developed code, using the statistical software R (43), to carry out a stratified random sampling of 50 of those clusters while maximizing the minimum nearest-neighbor distances between all clusters to try and minimize the risk of contamination (e.g., individuals from control clusters traveling to intervention clusters to receive the CDs). Specifically, the code randomly sampled 10 clusters per subdistrict, with the restriction that none of the CCs selected were within the following minimum distances of any other CC within their respective subdistrict: 3 km for the subdistricts of Barura, Brahman Para and Burichang and 2.5 km for the subdistricts of Daudkandi and Homna. These minimum nearest-neighbor distances were maximized by iteratively running the sampling code and increasing the minimum-allowed nearest-neighbor distance for each subdistrict, in steps of 0.5 km, while ensuring that there were still ≥10 CCs available per subdistrict from which 10 were then randomly sampled per subdistrict. Table 1 gives the key numerical details of the cluster sampling process.

**Table 1 tab1:** Subdistrict-specific number of community clinics, maximum nearest-neighbor distance between community clinics used when sampling clusters, and number of remaining community clinics left once restricted by the maximum possible nearest-neighbor distance that still left ≥10 community clinics in the subdistrict.

Subdistrict	Total number of CCs	Minimum distance between CCs in restricted population	Number of CCs remaining for final selection of 10 clusters
Barura	29	3 km	15
Brahman Para	20	3 km	12
Burichang	24	3 km	13
Daudkandi	22	2.5 km	15
Homna	21	2.5 km	15

CCs, community clinics.

#### Cluster recruitment and consent

We will seek written or verbal consent for the participation of clusters from both the upazila chairman (the elected local government representative of the subdistrict) of each subdistrict and the union parishad chairmen (the elected local government representatives of each union within each subdistrict, where unions are the administrative level below a subdistrict in local government). We will seek this consent during subdistrict level trial sensitisation meetings, which we will hold in each subdistrict prior to sampling and randomizing clusters.

#### Participant sampling

We will collect all trial data via a baseline and an endline household survey within the selected clusters in each subdistrict (see *Trial schedule*). For the household survey we will use a pragmatic, multi-stage sampling approach to select participants, based on the older WHO EPI cluster sampling method informally referred to as the “spin the pen” method (9). Note that although the intervention will be run across all villages within each intervention cluster, we will only collect trial data from participants living in two (or potentially just one) village. Specifically, based on our sample size calculation, within each cluster we will aim to sample 22 participants from the village that the cluster CC is located within and a further 22 participants from the next nearest village in that same cluster (or if there is just one village in the cluster then all 44 participants will be selected from that village).

To sample participants from each selected village our data collection team will locate the approximate center of the village (using local knowledge as necessary) and then spin a pen on the ground to select a random direction. They will then walk a transect in that direction, sketch mapping all households immediately either side of that transect line until they reach the edge of the village. They will then number all the sketched households and, using a random number table, select a random household from those listed. They will then go to that household, locate the first available eligible individual, inform them about the study and seek their consent to participate in that survey round. If they agree they will then interview them. They will then locate the next nearest household, followed by the next nearest household in relation to that one, and so on, until they reach the fifth next nearest household from the one previously sampled.

They will then sample and interview the first available eligible individual at this household who is of the opposite sex to the first participant. This sex switching will then be repeated for each subsequent participant. This is to maintain an approximate 1:1 sex ratio. Although the sex ratio in the population being sampled should be approximately equal without this process we may end up with a moderate to large sex imbalance depending on the availability of females vs. males during the surveys. They will then repeat this household skipping selection process, while avoiding households they have previously sampled, until they have selected the required number of participants for that village.

If an eligible individual declines to participate then they will try and recruit another eligible individual in that household or move onto the next nearest household. This approach clearly does not mitigate against sampling bias due to differential participation, and this may affect the generalisability of the results, but it does maintain the target sample size and power. Where it is not possible to sample 22 or 44 individuals from separate households based on the household skip pattern, due to a lack of households, they will modify the skip pattern accordingly.

#### Participant recruitment and consent

Our data collectors will attempt to recruit the household members that they sample into the study, as part of either survey, after explaining the study to them and providing them with the trial information sheet (if they are literate). If they agree to participate, they will then seek consent to both participate in the trial via the survey and to allow us to make their anonymised data, collected during the survey, freely available for research purposes via a public research data repository.

### Randomization

The trial statistician ([name]) will randomize all sampled clusters to the intervention or control groups in an overall 1:1 ratio using a stratified and restricted approach (44). This will involve stratifying the randomization by randomizing clusters within each subdistrict separately in a temporally staggered, subdistrict-by-subdistrict sequence (see *Trial schedule*) for logistical reasons. Within each subdistrict we will simultaneously randomize the 10 sampled study clusters within that subdistrict in a 1:1 ratio (i.e., 5 per treatment group) using a restricted approach, which aims to balance (across treatment groups) the baseline cluster-level values of the first (primary outcome) percentage knowledge score regarding correct and appropriate knowledge about antibiotics, ABR, and usage of antibiotics for human illness. Given that we are randomizing relatively few clusters, this randomization approach will increase the chances of obtaining an effective balance between treatment groups in terms of both the expected endline primary outcomes under the counterfactual that the intervention is not applied, as well as other observed and unobserved characteristics that are strongly causally related to at least the primary outcomes (44).

Specifically, using the baseline survey data for each cluster we will first compute the baseline cluster-level mean percentage knowledge score from the percentage knowledge scores of all survey participants in that cluster. Following the approach described by (44), we will then develop R code to randomize the clusters in one subdistrict at a time subject to the following restriction. For any given subdistrict the code will first enumerate every possible way the 10 clusters in the subdistrict can be allocated between the treatment groups in a 1:1 ratio. Within each subdistrict there are ^10^C_5_ = 252 possible ways to allocate the 10 clusters in a 1:1 ratio. The code will then look at each of those allocations and for each allocation it will compute the mean of the cluster-level mean percentage knowledge scores for the clusters allocated to each treatment group, and the difference between those treatment group means. Lastly, it will randomly select one of the possible allocations where the difference between the treatment group means is ≤ ± 5 percentage points (i.e., where the means of the cluster-level mean percentage knowledge scores are similar between the treatment groups at baseline).

We will verify the validity of this restricted randomization process in two ways. First, for each subdistrict we will test whether the restricted randomization process has resulted in a sufficiently large set of possible allocations (out of the maximum 252 possible allocations) to allow a meaningfully random selection, by looking at the percentage of allocations among the 252 that satisfied the restriction criteria and were available for random selection (44). If this is less than 50% (126) we will relax the restriction criteria by allowing the chosen allocation to be selected from the set of allocations where the restriction criteria difference is ≤ ± 10 percentage points. If there are still less than 50% of the original allocations available to select from we will iteratively further increase the allowed restriction criteria difference by ±5 percentage point increments until 50% or more of the total possible allocations are available.

Second, for each subdistrict we will look at all the allocations that satisfy the restriction criteria and compute how often each pair of clusters are present in either the same or opposite treatment groups (44). If one or more pairs of clusters co-occur in the same treatment group ≥80% of the time across the available allocations then we will again relax the restriction criteria by allowing the selection to include allocations where the restriction criteria difference is ≤ ± 10 percentage points. Again, if this test still fails after relaxing the criteria as described we will iteratively further increase the allowed restriction criteria difference by ±5 percentage point increments until one or more pairs of clusters co-occur in the same treatment group <80% of the time.

### Masking

Due to the nature of the intervention, it is not possible to mask participants, those running the intervention or members of the research team to the allocation of clusters. However, the data collectors will explicitly not be informed about randomization outcomes for the villages they work in. It is perfectly plausible though that they will become aware of the treatment status of villages by talking to participants, who will clearly likely be aware if they are in an intervention village.

